## Abstract

**Background:**

In Germany, a multidisciplinary rehabilitation named “behavioural medical rehabilitation” (BMR) is available for treatment of chronic low back pain (clbp). A central component of BMR is standard exercise therapy (SET), which is directed mainly to improve physical fitness. There is a need to address psychosocial factors within SET and therefore to improve behavior change with a focus on the development of self-management skills in dealing with clbp. Furthermore, short-term effectiveness of BMR with a SET has been proven, but the impact of a behavioural exercise therapy (BET) for improvement of the long-term effectiveness of BMR is unclear.

**Methods/design:**

To compare the effectiveness of two exercise programs with different approaches within BMR on the effects of BMR a prospective randomized controlled trial (RCT) in two rehabilitation centres will be performed. 214 patients aged 18–65 with clbp will be, based on an "urn randomisation"-algorithm, randomly assigned to a BMR with SET (function-oriented, n=107) and BMR with BET (behaviour-oriented, n=107). Both exercise programs have a mean duration of 26 hours in three weeks and are delivered by a limited number of not-blinded study therapists in closed groups with six to twelve patients who will be masked regarding study group. The main differences of BET lie in its detailed manualised program with a theory-based, goal-orientated combination of exercise, education and behavioural elements, active participation of patients and consideration of their individual preferences and previous experiences with exercise. The primary outcome is functional ability assessed with the Hannover Functional Ability Questionnaire directly before and after the rehabilitation program, as well as a six and twelve-month follow-up.

**Discussion:**

This RCT is designed to explore the effects of BET on the effectiveness of a BMR compared to a BMR with SET in the management of patients with clbp. Methodological challenges arise from conducting a RCT within routine health care as well as from ensuring high treatment integrity. Findings of this study might contribute to a better understanding of the mechanism of action of BMR and the special effects of BET and may be used to improve the quality of these interventions in routine care, therefore reducing the burden to patients with disabling clbp.

**Trial registration:**

Current controlled trials NCT01666639

## Background

Non-specific low back pain is one of the leading health problems regarding its medical and economic impact worldwide [1-4]. This is also the case in Germany with high substantial economic burden of an estimated €48.96 billion total costs related to low back pain for the entire German adult population aged 18 to 75 [5,6].

While the lifetime prevalence of low back pain is reported to be up to 84%, little scientific evidence is available for the prevalence of disabling chronic low back pain [4,7]. In a multiregional survey in the adult population in Germany reported more than 11% disabling chronic low back pain [5]. Clbp is also one of the most frequent conditions in traditional multidisciplinary inpatient rehabilitation in Germany [8].

Intensive multidisciplinary rehabilitation is recommended as first-line treatment for the management of disabling clbp [4,7,9]. It has been proven to be effective in the short term regarding pain intensity and functional disability compared to no treatment or waiting list controls [10]. But, there is a lack of evidence regarding the long-term effectiveness of such programs. Behavioural medical rehabilitation (BMR) in Germany is an intensive multidisciplinary inpatient rehabilitation program with a theory-based biopsychosocial approach [11]. In contrast to the traditional multidisciplinary inpatient rehabilitation, BMR is explicitly directed at orthopedic patients who show significant psychosocial risk factors for the chronification of musculoskeletal disorders. In a randomised controlled trial, the BMR had a positive short-term effect on depression and sustainable effects on several pain coping competencies [12] compared to traditional inpatient rehabilitation. A meta-analysis of intensified multidisciplinary inpatient rehabilitation for patients with musculoskeletal disorders [13] proved BMR to be superior to usual care regarding a sustainable improvement of the subjective health status. Evidence of long-term effects of BMR on pain and functional disability is lacking. It is also not yet clear which treatment component or combination of treatment components of an intensified rehabilitation regime explains the amount of variance regarding the effects in patients with disabling clbp [14].

A corner-stone is SET, which represents approximately 70% of all interventions within multidisciplinary rehabilitation, received by orthopedic patients in Germany [15]. SET is mainly based on a functional approach with methods to improve physical fitness [15,16]. Evidence shows that SET compared to usual care improves pain and function in patients with clbp, however the reported effect-sizes are low [17,18].

There is also evidence available confirming that psychosocial factors play a pivotal role in the development of clbp [19-21]. Addressing them specifically within exercise therapy might reduce obstacles to recovery and increased function [22,23]. Especially to improve self-management of back pain and the long-term adherence to regular physical activity [24], a broader theory-based approach with appropriate tools and strategies used by physical therapists within SET seems necessary [25,26]. An integration of biopsychosocial education and behavior change as well as the consideration of patients’ individual preferences and the realisation of positive experiences with physical activity seem to be superior to a solely functional approach [17,18,24,26-30].

An enhancement of long-term adherence to physical activity in chronically ill adults via patient-oriented methods directed at motivation and volition (e.g. planning) has been effective [27,31,32]. Conn et al. [27] detected behavior change interventions being effective across medical conditions (effect size 0.45) and showed an average increase in the amount of performed physical activity, which was 48 minutes higher than the increase in the control groups. The Review of Jordan et al. [24] examining interventions to improve exercise adherence in musculoskeletal disorders outlined that adherence is not influenced by the kind of exercise being performed (e.g. strength training, endurance-oriented activities). A combination of exercise with cognitive and behavioural strategies seems to be more important to improve adherence to physical activity or exercise and the addition of volitional methods to motivational methods is paramount [24,27,31-33].

There has not been in-depth research about the biopsychosocial effects of theory-based exercise therapy with a behavioural approach, named behavioural exercise therapy (BET), as part of the BMR in the management of disabling clbp. So the impact of a BET for improvement of the effectiveness of BMR is unclear.

### The aims of this study

Therefore the aims of this study are a) the development and implementation of a BET into an existing BMR and b) the evaluation of the effectiveness of BMR with BET compared to BMR with SET in routine health care (short-, mid-, and long-term effects) in the management of patients with disabling clbp.

## Methods/design

### Study design

To evaluate the effects of BET on the effectiveness of a BMR, a multicentre-study with a prospective randomised controlled design is conducted. This study takes place in two inpatient rehabilitation centres in Germany. Participants with clbp will be randomised into either a) the usual BMR with the SET as the control group (CG) or b) the BMR with the extended BET as the intervention group (IG) (see Figure 1). Primary and secondary outcomes will be measured by questionnaires directly before and at the end of the BMR (after approx. four weeks), as well as six and twelve months after completion of the BMR. The following figure shows the study design with appropriate study phases as well as the expected duration (see Figure 2).

**Figure 1 F1:**
[figure not shown]
Study Flow Diagram.

**Figure 2 F2:**
[figure not shown]
Study phases and expected duration.

### Hypotheses

#### Primary hypothesis

In patients with clbp, treatment with BMR+BET will result in a significantly higher increase in functional ability directly at the end, as well as six and twelve months after completion of BMR+BET compared to usual BMR+SET.

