### Sample size and power calculation

Thinking of the short-term effectiveness of both interventions, only small differences between groups and small effect sizes at the end of rehabilitation (t2) (d=0,3 or f(V)=0,15) are expected to be found [12,41,42]. Because of the minor long-term effects of the present usual care, medium effect sizes (d=0,5 or f(V)=0,25) are expected to be found at six and twelve months. This is in line with Friedrich and colleagues [43,44], who were able to show medium effect sizes regarding a reduction of disability when comparing a functional exercise therapy to an exercise therapy which contained additional motivational strategies (Disability Score: d~0,68). Sample power (Software: G-Power 3.0) concerning the primary outcome was approximated for an analysis of covariance at t4 with medium effect size of Cohen’s d=0,5, alpha error 5% and test power of 80%. This approximisation results in a sample size of at least 128 patients without missing values. Anticipating a dropout rate of 40%, it is necessary to include 214 patients (n=107 for each group).

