#### Primary outcome measure

We will use the level of functional limitations associated to clbp twelve months after the end of BMR measured by the Hannover Functional Ability Questionnaire (FFbH-R) as our primary outcome [51]. The FFbH-R consists of twelve items with a three-stage answering scale. Its summary score describes the low back pain associated functional ability in activities of daily living in adults on a scale of 0% (minimum functional ability) to 100% (maximum functional ability). The questionnaire is constructed for response to already light and moderate functional restrictions. The average item intercorrelation amounts to 0.50. The test-retest-reliability with repeated measures after approximately one week is above 0.75, Cronbach alpha figures 0.90 [51]. The one factorial structure of the instrument was confirmed in a principal component analysis. The FFbH-R is comparable to the internationally used Roland Morris Questionnaire for measuring clbp related disability with a correlation of 0.75 [73].

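### The protocol states its primary claim in three incompatible ways, and the 80% power applies to the twelve-month comparison, not to the claim at the end of rehabilitation

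*Protocol article*

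**What the plan says.** Five places in the protocol article bear on the primary claim.

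- **Hypotheses, Primary hypothesis:** BMR+BET is to give a "significantly higher increase in functional ability directly at the end, as well as six and twelve months after completion of BMR+BET". This is one primary claim covering three time points (t2, t3, t4). The secondary hypotheses that follow do not list short-term or six-month function.
- **Outcome assessment, Primary outcome measure:** the primary outcome is the "level of functional limitations associated to clbp twelve months after the end of BMR", a single time point.
- **Sample size and power calculation:** "small effect sizes at the end of rehabilitation (t2) (d=0,3 or f(V)=0,15) are expected to be found", whereas "medium effect sizes (d=0,5 or f(V)=0,25) are expected to be found at six and twelve months". Power is worked out only for an analysis of covariance at t4 with d = 0.5, alpha 5% and power 80%. This gives 128 patients without missing values, or 214 after 40% dropout.
- **Data analysis:** the main test compares, by likelihood ratio, a mixed model with group-by-time interactions against a nested model without them. Comparing the two groups' slopes in each of the two phases is an additional step.
- **Abstract, Methods/design:** function is measured "directly before and after the rehabilitation program, as well as a six and twelve-month follow-up", with no time point singled out.

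**The concern.** The hypothesis, the outcome definition and the planned test should describe the same comparison, and here they describe three. A trial positive at t4 but not at t2 would succeed under the outcome section and fall short of the hypothesis as worded. A trial with a significant overall interaction but no clear difference at t4 would succeed under the analysis section and fail under the outcome section. Without one stated claim, the choice could be made after the results are known.

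Power is affected too. The hypothesis includes t2, where the plan itself expects a smaller effect than the one used to size the trial. A reader who takes the 80% as the chance of confirming the primary hypothesis would be misled.

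**Working it through.** **Inputs, all from Sample size and power calculation:** d = 0.3 at t2; d = 0.5 at t3 and t4; alpha 5%; 128 evaluable (64 per arm); 214 randomised (107 per arm); 40% dropout. Sidedness is not stated; two-sided reproduces the plan's figure and is used throughout.

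**1. The plan's own figure.** For a two-sided t test with n per arm, the noncentrality is d × √(n/2), with 2n − 2 degrees of freedom.
- n = 64, d = 0.5: 0.5 × √32 = 2.83, critical value 1.98, power 0.801.
- n = 63: power 0.795, so 64 per arm (128) is the smallest that reaches 80%. The F test for an analysis of covariance with f = 0.25 and one covariate also gives 0.801 at 128.
- Dropout: 128 / (1 − 0.40) = 213.3, rounded up to 214.

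The sample size for t4 is correct. It also covers t3 numerically, because t3 shares d = 0.5.

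**2. The same formula at t2, d = 0.3.**
- n = 64: 0.3 × √32 = 1.70, power 0.391.
- n = 107: 0.3 × √53.5 = 2.19, power 0.589.
- 80% power needs 176 per arm, or 352 evaluable. At 40% dropout that is 352 / 0.60, or 587 randomised.

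The dropout rate is not split by time point. By normal approximation, t2 power is 40% with 40% missing, 45% with 30%, 50% with 20%, 55% with 10% and 59% with none.

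**3. If significance were required at all three points** (effects 0.3/0.5/0.5; simulated trivariate normal test statistics). The correlation between the statistics is not in the protocol, so it is assumed, over a range of 0 to 0.9.

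| Correlation | 64 per arm | 107 per arm |
|---|---|---|
| 0 | 26% | 54% |
| 0.5 | 35% | 58% |
| 0.7 | 38% | 59% |
| 0.9 | 40% | 59% |

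**4. If any one point at two-sided 5% were accepted.** Family-wise error is 1 − 0.95³ = 14% for independent statistics, falling to 12%, 11% and 8% at correlations 0.5, 0.7 and 0.9.

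**5. A single overall test.** As an approximation to the planned likelihood ratio test, take a 3-degree-of-freedom test of any group difference over t2–t4. Its noncentrality is (n/2) × δ′C⁻¹δ, with δ = (0.3, 0.5, 0.5) and C an equal-correlation matrix. With 64 per arm:
- correlation 0.29: noncentrality 12.6, power 86% (chi-square) or 85% (F);
- correlation 0.41: 11.4, power 82% or 80%;
- correlation 0.5: 10.7, power 79% or 78%;
- correlation 0.7: 10.4, power 78% or 76%.

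The spline form in Data analysis may use fewer degrees of freedom. Power for this test is thus near 80% over these correlations, but a significant result would not say at which time point the groups differ.

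**The case against.** The strongest reply is that the protocol plans one overall test. On that view there is no multiplicity problem and, by step 5, power is close to the stated 80%. This stands as far as it goes. A reader might infer that the false-positive rate is well above 5%, or that the primary claim will probably fail. The documents support neither as a statement about the planned analysis. They contain no three separate tests at 5%, no rule that any one suffices, and no rule that all three must be significant. The figures in steps 3 and 4 are conditional on such rules. The reply does not remove the inconsistency, however. The overall test is not the t4 comparison that was powered, and rejecting it establishes neither a twelve-month effect nor superiority at each time point.

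Second, the outcome and sample size sections agree on t4, and the plan openly expects a small effect at t2. That is true, and it is why t4 is the natural single claim. But the text headed as the primary hypothesis still asserts three time points.

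Third, the abstract might be read as making every time point co-primary. Its list includes the baseline assessment, so it reads better as a measurement schedule. It needs clarifying but is not a separate contradiction.

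Fourth, 39% is the low end for t2. Those questionnaires are collected at the end of the inpatient stay, so fewer may be missing there than in the postal follow-up; hence the range to 59%. Baseline adjustment could raise power if d is on the raw-score scale. With an assumed baseline correlation of 0.5 it would be 50% (64 per arm) to 72% (107 per arm), and with 0.7 it would be 66% to 87%. The plan's t4 calculation takes no such gain, so the comparison here uses the plan's own scale.

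**Conclusion.** The inconsistency is in the current text and is real. The primary claim is superiority at t2, t3 and t4 in one section, the twelve-month score in another, and an overall interaction in a third. The t4 sample size is sound. What lacks support is the t2 part of the primary hypothesis, with power of about 39–59% on the plan's own d = 0.3, and hence the three-point claim taken as a whole. These figures assume a two-sided 5% test and d on the scale of the analysis, as in the plan. The joint-power figures also rest on assumed correlations. A family-wise error of about 8–14% would arise only under an any-of-three success rule that the protocol does not state. The point should be corrected because it decides what the trial's primary conclusion is.

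**What to change.** 1. **Primary hypothesis:** restate it as the group difference in FFbH-R at t4, in line with Primary outcome measure and the sample size.
2. **Data analysis:** make the baseline-adjusted group contrast at t4 the primary test, from the mixed model or the analysis of covariance. Make the overall likelihood ratio test and the t2 and t3 contrasts secondary, for example in a fixed order after t4. Without this step the hypothesis and the test would still not match.
3. **Abstract:** say that the other time points are assessments and not co-primary outcomes.
4. **Sample size and power calculation:** say that the 80% applies to t4 only.

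The cost is wording; no extra patients or measurements are needed. The downside is that the short-term claim becomes secondary.

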#### Secondary hypothesis

There are numerous interrelations between self-management of clbp, pain-related cognitions, physical activity, health-related quality of life and the number of back pain episodes [19,21,22,34-37]. For these reasons the following secondary hypotheses are tested:

In patients with clbp, treatment with BMR+BET, compared to usual BMR+SET, will result in a significant:

– Improvement of pain-related cognitions

– Increase of physical activity

– Improvement in health-related quality of life

– Decrease in back pain episodes

– Improvement in pain coping strategies

### Study population

Patients with clbp, who are invited consecutively in the two collaborating rehabilitation centres between January 2012 and January 2013, are eligible by reservation. Chronic non-specific low-back pain is defined as pain persisting for at least three months, localised below the costal margin and above the inferior gluteal folds, without referred leg pain and that is not caused by a known specific pathology [7]. Inclusion criteria are based on the international classification of diseases (ICD-10) in its German modification. Inclusion and exclusion criteria are described in Table 1.

**Table 1 T1:** Inclusion and exclusion criteria

**Inclusion**	**Main diagnosis for a BMR:**
criteria	-M51.2-M51.9 (other intervertebral disc disorders),
(ICD-10)	-M53.8, M53.9 (other specified/unspecified dorsopathies),
	-M54.4-M54.9 (lumbago with sciatica, low back pain, pain in thoracic spine, other/unspecified dorsalgia),
	-F45.4 (persistent somatoform pain disorder),
	-F45.41 (chronic pain disorder with somatic and psychological factors),
	-F54 (psychological and behavioural factors associated with disorders or diseases classified elsewhere)
Exclusion criteria	-specific underlying diagnosis of the back pain (e. g. radicular symptoms, myelopathy)
	-considerably reduced health status (comorbidities)
	-considerable reduction of sight and hearing
	-severe psychiatric condition as secondary diagnosis
	-age below 18 or over 65 respectively
	-lack of ability to speak German
	-ongoing application for retirement

### Recruitment procedures

After submission of the signed consent form of the study participants („informed consent“), patient enrollment takes place in the participating rehabilitation centres based on the assessment of the inclusion and exclusion criteria by the attending physician. Next, patients are randomly assigned to the different treatment groups.

The recruitment procedure is adjusted to each of the centre’s internal structures and processes regarding the invitation of patients.

In the rehabilitation centre “Paracelsus-Klinik an der Gande” potential study participants will be identified by a screening of the patient record by the head physician prior to the invitation to the BMR. Afterwards, eligible patients will obtain written patient information and a consent form about the study and will be asked to participate. After returning the signed consent form within seven days, the patients will be randomised online. The invitation of the randomised patients will take place weekly and in groups according to the group assignment in the respective week of arrival. At the beginning of the rehabilitation program, an information meeting will be held by the head physician for all eligible patients fully explaining the study.

In the rehabilitation centre “Klinik Weser” potential study participants will be identified at the beginning of the BMR in medical admission interviews and will obtain a written consent form. In an information meeting all eligible patients are fully informed about the study primarily by the head physician. On the second day, after returning the signed consent form, the online-based randomisation will take place. Due to spatial and personnel-wise requirements, one control and one intervention group will start simultaneously every fourteen days. Therefore, the recruitment of eligible patients will take place in a biweekly rhythm.

In both rehabilitation centres, the group size is limited to twelve participants. If the number of eligible study patients is too small for starting a control or intervention group, the participation of non-eligible patients who do not take part in the study is accepted to reach the necessary group size. At least 40 potentially eligible patients will be treated every month in both rehabilitation centres. Considering a recruitment rate of 60%, 358 eligible patients will have to be asked to participate in the study in order to achieve the required sample size. Based on the assumption that average closed groups consist of six to seven participants, the recruitment period is predefined as a period of twelve months. Both rehabilitation centres confirmed that a sufficient number of eligible patients would exist to achieve the necessary sample size in the study period.

The collection of consent forms, distribution and collection of questionnaires and the delivery of the latter to the study team are adjusted to the process of patient admission and discharge in standardised form. The process will be tested and automated in each of the rehabilitation centres during the phase of implementation.

